## Abstract

**Background:**

The optimal surgical management of dislocated three- and four-part fractures of the proximal humerus in elderly patients remains unclear. Most used techniques are hemiarthroplasty and angle-stable locking compression plate osteosynthesis. In the current literature there is no evidence available presenting superior results between hemiarthroplasty and angle-stable locking compression plate osteosynthesis in terms of speed of recovery, pain, patient satisfaction, functional outcome, quality of life or complications.

**Methods/Design:**

A randomized controlled multicenter trial will be conducted. Patients older than 60 years of age with a dislocated three- or four-part fracture of the proximal humerus as diagnosed by X-rays and CT-scans will be included. Exclusion criteria are a fracture older than 14 days, multiple comorbidity, multitrauma, a pathological fracture, previous surgery on the injured shoulder, severely deranged function caused by a previous disease, "head-split" proximal humerus fracture and unwillingness or inability to follow instructions. Participants will be randomized between surgical treatment with hemiarthroplasty and angle-stable locking compression plate osteosynthesis. Measurements will take place preoperatively and 3 months, 6 months, 9 months, 12 months and 24 months postoperatively. Primary outcome measure is speed of recovery of functional capacity of the affected upper limb using the Disabilities of Arm, Shoulder and Hand score (DASH). Secondary outcome measures are pain, patient satisfaction, shoulder function, quality of life, radiological evaluation and complications. Data will be analyzed on an intention-to-treat basis, using univariate and multivariate analyses.

**Discussion:**

Both hemiarthroplasty and angle-stable locking compression plate osteosynthesis are used in the current treatment of dislocated three-and four-part fractures of the proximal humerus. There is a lack of level-1 studies comparing these two most-used surgical treatment options. This randomized controlled multicenter trial has been designed to determine which surgical treatment option provides the fastest recovery of functional capacity of the affected upper limb, and will provide better outcomes in pain, satisfaction, shoulder function, quality of life, radiological evaluation and complications.

**Trial registration number:**

The trial is registered in the Netherlands Trial Registry (NTR2461)

## Background

Proximal humeral fractures account for approximately 5% of all fractures [1]. More than 70% of patients with these fractures are older than 60 years of age, 75% are women, and the fractures are often related to osteoporosis [2,3]. For this elderly population the goal of treatment of proximal humeral fractures is to maintain independence of daily living by achieving a painless shoulder with an adequate function.

The majority of proximal humeral fractures are non- or minimally displaced, and are well treated nonoperatively [4,5]. In displaced three-and four-part proximal humeral fractures surgical treatment is recommended [5,6]. However, the optimal surgical management remains controversial. A wide variety of treatment modalities, varying from minimal percutaneous osteosynthesis to prosthetic replacement of the humeral head, has been described. Besides a certain consensus regarding prosthetic treatment of "head-split" fractures [6,7], the surgical treatment of choice is based on preference toward and experience with one of the treatment options. Most comminuted proximal humeral fractures are currently being treated with placement of a hemi-shoulder prosthesis, or in case of treatment of the humeral head with an angle-stable locking compression plate.

Specially designed prostheses have been developed for treatment of dislocated three-and four-part proximal humeral fractures. Important is the refixation and healing of the tuberosities [8-10]. Several studies report good outcomes regarding function, level of patient satisfaction, pain and complication rate [10-13]. Factors associated with poor outcomes are: secondary prosthetic replacement after initial osteosynthesis, malunion, osteolysis of the tuberosities, and excessive retroversion of the prosthetic head or over-lengthening due to prosthetic placement [14-18].

In recent years the use of angle stable locking compression plates has been popularized. Biomechanical data suggest that these implants can resist physiological loads in osteoporotic bone and may provide an alternative to hemiarthroplasty [19-21]. Other theoretical advantages compared to conventional plating are a reduction in screw loosening, less dissection of soft tissue, less compromising of periosteal vascularization through minimal plate pressure, and an increased primary stability which enables early functional mobilization. The clinical utility of angle-stable locking compression plates for three- and four-part fractures of the proximal humerus remains unclear [22-24]. Substantial rates of complications have been reported. Factors associated with poor outcomes are: the degree of varus malreduction, length of the initial metaphyseal hinge attached to the articular fragment and its correlation with osteonecrosis of the humeral head and screw protrusion through the humeral head.

A recent review could not draw firm conclusions with regard to which interventions are the most appropriate to manage different types of proximal humeral fractures [25]. Moreover, there are no level-1 randomized studies that compare surgical treatment of displaced three- and four-part fractures of the proximal humerus using hemiarthroplasty with surgical treatment using an angle-stable locking compression plate. It is therefore unclear which treatment leads to a better functional result: surgical treatment performing hemiarthroplasty or humeral head treatment with an angle-stable locking compression plate.

We designed a multicenter randomized controlled trial to compare hemiarthroplasty with an angle-stable locking compression plate for the treatment of dislocated three- and four-part fractures of the proximal humerus in an older population. This paper reports the study design of the HOMERUS (**H**emiarthroplasty vs. **O**steosynthesis in Hu**ME**ral F**R**act**U**re**S**) study.

## Methods/Design

### Study design

The HOMERUS study is designed as a level-1 multicenter prospective randomized controlled trial. Four centers in the Netherlands will participate. Eligible patients attending the Emergency Room (ER) with a comminuted proximal humeral fracture will receive information about the trial at the ER. After written consent has been confirmed, eligible patients will be randomly allocated to the two different types of surgical treatment. To keep the allocation of patients in different clinics even, block randomization will be used. For every participating hospital an exclusive sequence will be used and every block will contain ten patients. Randomization will be accomplished via opaque, sealed envelopes. Follow-up will take place over a period of two years. The inclusion period is planned from January 2011 to December 2012. The study design, procedures, protocols and informed consent are approved by the Medical Ethical Committees of the participating hospitals. The trial is registered in the Netherlands Trial Registry (NTR2461), and is designed in accordance with the Declaration of Helsinki [26] and the Medical Research Involving Human Subjects Act. It will follow the CONSORT (Consolidation of Standards of Reporting Trials) guidelines [27,28].

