**Figure 2 F2:**
[figure not shown]
**Example of proximal humerus fracture, managed by angle-stable locking compression plate osteosynthesis**.

The surgical procedures will be performed by a maximum of three qualified and experienced surgeons at each participating hospital. Surgery will take place within 2 weeks after the date of trauma. In both groups the specific type of implant will be determined by the attending surgeon at hospital the patient has been admitted to. In both groups a standard deltopectoral approach will be used. Antibiotic prophylaxis with first-generation cephalosporin will be given intravenously, preoperatively and for 24 hours postoperatively. Postoperatively patients will receive thromboprophylaxis during hospital stay (e.g. Low Molecular Weight heparin (LMWH) or equivalent). In terms of rehabilitation, all patients will be treated with a standardized protocol at each hospital. After surgery, the patient receives a sling for six weeks combined with mobilization instructions. Two weeks postoperatively, active range of motion will be increased to the horizontal level; after another two weeks active external rotation will be initiated. Rehabilitation will be supervised by a physiotherapist.

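### A constant, published block of ten within each hospital makes about 15% of allocations deducible in advance by anyone who keeps count; undisclosed, randomly varying block sizes would remove most of that certainty

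*Protocol article*

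**What the plan says.** All of the allocation method stands in the Study design section of the protocol article.

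- Sites: "Four centers in the Netherlands will participate".
- Purpose of blocking: "To keep the allocation of patients in different clinics even, block randomization will be used".
- Structure of the list: "For every participating hospital an exclusive sequence will be used and every block will contain ten patients".
- Concealment: "Randomization will be accomplished via opaque, sealed envelopes".
- Timing: "After written consent has been confirmed, eligible patients will be randomly allocated to the two different types of surgical treatment".

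The Interventions section adds: "The surgical procedures will be performed by a maximum of three qualified and experienced surgeons at each participating hospital". The two arms are a cemented prosthesis and a plate with screws. The article mentions no variation in block size and describes no blinding. The Background section says that the choice of operation in practice depends on preference and experience. The exclusion criteria include one that rests on judgement, namely whether the patient is willing and able to follow instructions.

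**The concern.** If the block size is constant and known, and past allocations can be seen, the end of each block follows by subtraction. Once one arm has used its five places, every remaining place in that block belongs to the other arm. An opaque envelope hides its own content but not this deduction. Allocation after written consent does not close the gap either, because the decisions on whom to inform, invite or judge eligible are made earlier.

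At stake is selection bias. A clinician who prefers one operation and knows what comes next could, consciously or not, find a borderline patient unsuitable. The arms could then differ in prognosis, and an intention-to-treat analysis does not correct for that. The primary outcome is the DASH, a patient questionnaire on which a difference in frailty or motivation between arms would show directly.

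**Working it through.** **The plan's own figures.** The article gives no figure for predictability. The total it plans for is needed here, and it reproduces. With a difference of 10, an SD of 19.4, two-sided alpha of 5% and power of 80%, the normal formula gives 2 × (1.96 + 0.842)² × 19.4² / 10² = 59.1, rounded up to 60. The t-test version gives 60.06, rounded up to 61 as stated. Then 61 × 1.1 = 67.1, so 67 per group and 134 in total. The sample size is not affected by this point.

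**Inputs.** From Study design: block size 10, one sequence per hospital, four hospitals, 24 months of inclusion. From Sample size: 134 patients. Assumptions: 5:5 within each block (the ratio is not written out, but the aim is even allocation and the groups are equal); equal recruitment per hospital; an observer who knows the block size and tallies every allocation from the first patient.

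**Certain allocations per complete block.** The certain allocations are those in the final run of one arm. With m = 5 per arm, the mean length of that run is 2m/(m + 1) = 10/6 = 1.67, or 16.7% of the block. Enumerating all C(10,5) = 252 blocks agrees:

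| Length of final run | Blocks | Share |
|---|---|---|
| 1 | 140 | 55.6% |
| 2 | 70 | 27.8% |
| 3 | 30 | 11.9% |
| 4 | 10 | 4.0% |
| 5 | 2 | 0.8% |

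So at least one allocation is certain in every complete block, and at least two in 112/252 = 44.4%.

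**Scaled to the trial.**

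- 134/4 = 33.5 patients per hospital, or 33.5/24 = 1.4 per month. That is easy to tally.
- With 34 patients there are three complete blocks and four patients over. The last four cannot be certain, because five of one arm must come first. The share is 3 × 1.67/34 = 5/34 = 14.7%.
- Depending on how 134 patients split over four hospitals, there are 10 to 13 complete blocks. Counting complete blocks only, 10 × 1.67 = 16.7 and 13 × 1.67 = 21.7, so about 17 to 22 patients (12% to 16%).

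**Other fixed sizes.** By the same formula the certain share is 33.3% for blocks of 4, 25.0% for 6 and 20.0% for 8. A smaller fixed block would be worse.

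**Varying sizes.** The comparison simulates 34 patients per hospital. The observer knows the set of sizes and updates the probabilities after each allocation.

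| | Fixed 10 | 6, 8, 10, 12 in random order |
|---|---|---|
| Certain | about 15% | about 1% |
| Predictable above 90% | about 15% | about 2% |
| Predictable above 80% | about 15% | about 10% |
| Best guess correct | about 64% | about 65% |

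The change removes certainty. It does not lower the average accuracy of guessing.

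**The case against.** The strongest case on the other side has five parts.

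- **The gain can be oversold.** A reader might infer from the fall from 15% to 1% that foreknowledge is nearly abolished. It is not. The best-guess rate does not fall, and a clinician with a preference can act on odds of 80% to 90%. This stands, and the smaller gains must be reported beside the large one.
- **Ten is already a fairly large block.** A reader might infer that several allocations are known at the end of each block. In 56% of blocks only the final one is. This stands.
- **Some links are inferences.** The article limits the number of operating surgeons. It does not say that each sees every allocation, who enrols, or who opens the envelopes. It is silent on blinding. That the operating team knows the procedure is a safe inference; that patients and assessors are unblinded is not stated. Nor does anything show that staff would keep a tally. This stands, so the figures describe what could be deduced, not what will happen.
- **Holding a patient back is hard.** Fractures older than 14 days are excluded and surgery must follow within two weeks. At 1.4 patients per month, the next patient at a hospital comes on average after about three weeks. Most criteria (age, displacement on CT, ASA class, injury severity) are fairly objective. This stands largely, but the judgement on following instructions remains a usable route.
- **Who makes and holds the lists is not described.** A condensed article may leave that to the full protocol, so it is no finding here.

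A reader might also infer that no analysis could repair the damage. That is too absolute: measured baseline differences, including the assessment at randomization, can be adjusted for. Unmeasured selection cannot.

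**Conclusion.** The point holds as a moderate weakness in something the article itself fixes. It is not a detail left to another document: a single constant block size is stated and published, and any fuller document would have to contradict the article to remove the problem. Under the assumptions of 5:5 blocks and an observer who keeps count, about one allocation in seven is known beforehand. The mechanism, the stated role of surgeon preference and one exclusion criterion based on judgement together leave a route to selection bias that the stated safeguards do not close. The documents do not support a claim that bias has occurred or is likely. The change should be made because it costs little, not because the trial would be invalid without it.

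**What to change.** Keep a separate sequence for each hospital. Replace the constant block with sizes in random order around the present one, for example 6, 8, 10 and 12, and do not disclose the sizes to the hospitals. Apply this to the whole list if no patient has been randomized, and otherwise to all blocks not yet opened. In the protocol, state that block sizes vary and are withheld from the sites, without listing them.

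The cost is a new randomization list and slightly more chance imbalance in the last incomplete block at each hospital. Sample size, follow-up and the surgical procedures are unchanged.

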### Study population

All patients attending the ER with a three- or four-fragment fracture of the proximal humerus with dislocation on X-ray and who are older than 60 years of age will undergo further CT-scan examination. If the CT-scan shows more than 5 mm dislocation in one of the fracture planes [29], the patient is eligible for inclusion [table 1]. Patients with a fracture more than 14 days old, multiple comorbidity, multitrauma (Injury Severity Score > 15), pathological fracture, previous surgery on the injured shoulder, severely deranged function caused by a previous disease, head-split proximal humerus fracture [6,7], or unwillingness or inability to follow rehabilitation instructions are excluded.

**Table 1 T1:** Inclusion and exclusion criteria

Inclusion criteria
3- and 4-fragment fracture of the proximal humerus
> 5 mm dislocation in one of the fracture planes
> age 60 years

**Exclusion criteria**

Fracture older than 14 days
ASA IV-V
Multitrauma ISS > 15
Pathological fracture
Previous surgery on injured shoulder
Severely deranged function caused by a previous disease
"Head split" type fracture of proximal humerus
Unwillingness or inability to follow instructions

### Interventions

Patients will be randomized to either hemiarthroplasty or angle-stable locking compression plate osteosynthesis.

Hemiarthroplasty [Figure 1] will be performed using the fracture shoulder prosthesis as provided at the participating hospital. A standardized deltopectoral approach with the patient in beach-chair position is used. After identification of the greater and lesser tuberosities, strong non-absorbable sutures are placed through the bone-tendon junctions. The head fragment is taken out and preserved for prosthetic head measurement. The humeral shaft is prepared for the specific implant. Humeral length is restored and the prosthesis is cemented in approximately 20-30 degrees retroversion. Tuberosity positioning is performed with the use of nonabsorbable sutures to attach the fragments to the prosthesis, the shaft, and to each other in an anatomic position.

**Figure 1 F1:**
[figure not shown]
**Example of proximal humerus fracture, managed by hemiarthroplasty**.

Angle-stable locking plate osteosynthesis [Figure 2] is performed with the patient in supine or beach-chair position on a radiolucent table and a deltopectoral approach is used. The fracture is reduced and provisionally stabilized with (threaded) Kirschner wires. The reduction is confirmed as adequate with use of image intensification. The angle-stable locking compression plate is positioned with the help of a mounted aiming device, at least 5-8 mm distally of the upper end of the greater tuberosity and 2 mm posteriorly to the bicipital groove. Care is taken to ensure that a sufficient gap is maintained between the plate and the tendon of the long head of the biceps. When fracture reduction and subsequent screw positioning is considered adequate, the plate is fixed definitively with the insertion of angular stable screws in the humeral head. The use of angular stable or standard cortical screws for the humeral shaft holes is left to the treating surgeon. A final image intensifier check to verify correct screw placement is performed.

**Figure 2 F2:**
[figure not shown]
**Example of proximal humerus fracture, managed by angle-stable locking compression plate osteosynthesis**.

The surgical procedures will be performed by a maximum of three qualified and experienced surgeons at each participating hospital. Surgery will take place within 2 weeks after the date of trauma. In both groups the specific type of implant will be determined by the attending surgeon at hospital the patient has been admitted to. In both groups a standard deltopectoral approach will be used. Antibiotic prophylaxis with first-generation cephalosporin will be given intravenously, preoperatively and for 24 hours postoperatively. Postoperatively patients will receive thromboprophylaxis during hospital stay (e.g. Low Molecular Weight heparin (LMWH) or equivalent). In terms of rehabilitation, all patients will be treated with a standardized protocol at each hospital. After surgery, the patient receives a sling for six weeks combined with mobilization instructions. Two weeks postoperatively, active range of motion will be increased to the horizontal level; after another two weeks active external rotation will be initiated. Rehabilitation will be supervised by a physiotherapist.

### Measurements

Outcome assessment will take place in both groups at randomization (T0), 3 months postoperatively (T1), and 6, 9, 12 and 24 months (T2, T3, T4, T5) postoperatively. Outcome assessment for T0, T1, T4 and T5 will take place in an outpatient clinic setting and involves all outcome measures. At six and nine months postoperatively (T2 and T3) patients will only fill in a questionnaire that will be sent and returned by mail [Figure 3]. Speed of recovery of functional capacity of the affected upper limb is our primary outcome measure. Secondary outcome measures are pain, patient satisfaction, shoulder function, quality of life, radiological evaluation and complications.

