## Discussion

Both hemiarthroplasty and angle-stable locking compression plate osteosynthesis for dislocated three-and four-part fractures of the proximal humerus in the elderly are performed in current practice. The optimal surgical management remains controversial and a clear distinction between indications for one of both treatment options cannot be made on the basis of the current evidence in the literature. To date, there are no randomized controlled studies that compare the outcome of hemiarthroplasty vs. angle-stable locking compression plate osteosynthesis in the treatment of dislocated three- and four-part fractures of the proximal humerus. The HOMERUS study is designed to determine which treatment results in better outcome, defined as speed of recovery of functional outcome. Further, it is possible to identify which treatment will provide better outcomes in pain, satisfaction, shoulder function, quality of life, radiological evaluation and complications.

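### Speed of recovery on the DASH is the primary outcome, but no DASH is scheduled between T0 and 3 months, so the shape of early recovery is not observed

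*Protocol article*

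**What the plan says.** The Measurements section states: "Speed of recovery of functional capacity of the affected upper limb is our primary outcome measure". The abstract names the instrument: "Primary outcome measure is speed of recovery of functional capacity of the affected upper limb using the Disabilities of Arm, Shoulder and Hand score (DASH". The abstract's discussion says that the trial is meant "to determine which surgical treatment option provides the fastest recovery of functional capacity of the affected upper limb", and the main Discussion asks "which treatment results in better outcome, defined as speed of recovery of functional outcome". Speed is therefore the declared question throughout.

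The schedule is given twice and agrees. Measurements places assessments "at randomization (T0), 3 months postoperatively (T1), and 6, 9, 12 and 24 months (T2, T3, T4, T5) postoperatively". The abstract says: "Measurements will take place preoperatively and 3 months, 6 months, 9 months, 12 months and 24 months postoperatively". T2 and T3 (6 and 9 months) are questionnaires sent and returned by mail; the other assessments are clinic visits.

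The Interventions section sets out the rehabilitation: "After surgery, the patient receives a sling for six weeks combined with mobilization instructions". Active range of motion is raised to the horizontal at two weeks, and active external rotation follows two weeks after that. No functional measurement is described during this period, and no reason is given for starting at 3 months.

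**The concern.** A speed outcome depends on when the curve is sampled. If one operation returns function sooner but both groups reach the same level by month 3, the planned assessments would show no difference, although the answer to the stated question would be that one operation is faster. The three rehabilitation steps that the article describes (2, 4 and 6 weeks) all lie in the unmeasured window, so the groups could plausibly differ there.

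This is not a detail that a fuller protocol or an analysis plan could supply. The schedule is stated explicitly in two places, and no later analysis can recover scores that were never collected. The random effect models named under Statistical analysis can only interpolate between T0 and T1.

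**Working it through.** **Inputs from the article.** Sample size section: difference 10 DASH points (set at 24 months), SD 19.4, alpha 5%, power 80%, 61 per group, 67 per group after 10% dropout. Measurements section: T0, then 3, 6, 9, 12 and 24 months.

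**1. The plan's own figure.** n per group = 2 × [SD × (1.960 + 0.842) / 10]² = 2 × (19.4 × 2.802 / 10)² = 59.1, so 60 by the normal approximation. The t-test version gives 60.06, so 61. This reproduces the stated 61 with a two-sided test; a one-sided test gives 47. For dropout, 60 / 0.9 = 66.7, so 67, as stated (61 / 0.9 gives 68). The sample size arithmetic is not at issue here.

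**2. Count of assessments.** Between surgery and month 3: 0. From month 3 to month 24: 5. T0 and T1 bracket the early window, so its net change is known and its shape is not.

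**3. What could be lost: an illustration on assumed curves.** The article gives no early DASH values. Assume that both groups recover exponentially from a starting DASH B to a common plateau of 40, one group twice as fast, with B between 60 and 80. The group difference at t months is

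d(t) = (B − 40) × [2^(−t/h2) − 2^(−t/h1)],

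where h1 and h2 are the half-recovery times. The largest gap occurs at t = h2. In each cell the first figure is for B = 60 and the second for B = 80.

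| Half-recovery (months) | Largest gap | Gap at 3 months | Gap at 6 months |
|---|---|---|---|
| 0.5 vs 1 | 5.0 to 10.0 at 1 month | 2.2 to 4.4 | 0.3 to 0.6 |
| 1 vs 2 | 5.0 to 10.0 at 2 months | 4.6 to 9.1 | 2.2 to 4.4 |
| 2 vs 4 | 5.0 to 10.0 at 4 months | 4.8 to 9.6 | 4.6 to 9.1 |

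Worked cell: B = 80, 0.5 vs 1, t = 3: 40 × (2^−3 − 2^−6) = 40 × (0.1250 − 0.0156) = 4.4.

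**4. Power at T1.** The standard error of a difference at one visit is 19.4 × √(2/61) = 3.51 (SD assumed the same at every visit). By the normal approximation, a gap of 2.2 has about 9% power and 4.4 about 24%. For 1 vs 2 months the T1 figures are about 26 to 74%, and for 2 vs 4 months about 28 to 78%. In the fastest case T1 keeps 2.2 / 5.0 = 44% of the largest gap; in the other two it keeps 91% and 96%.

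**5. What an added visit would show.** In the fastest case the gap at 6 weeks (t = 1.5) is 4.6 to 9.1 points, with single-visit power of about 26 to 74%, against 9 to 24% at T1.

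**6. Why the form of the model matters.** Take a 10-point difference at 6 weeks only and none later, six postoperative visits (1.5, 3, 6, 9, 12, 24 months), 61 per group, SD 19.4, and an assumed within-patient correlation of 0.5.
- Average over visits: difference 10/6 = 1.67, standard error 19.4 × √(3.5/6) × √(2/61) = 2.68; power about 10%.
- Linear slope: sum of squared time deviations 334.9, slope difference 7.75 × 10 / 334.9 = 0.231 per month, standard error 19.4 × √(0.5/334.9) × √(2/61) = 0.136; power about 40%.
- Group-by-visit test, 5 df: noncentrality 100 × (5/6) / (19.4² × 0.5 × 2/61) = 13.5; power about 82%.

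An added visit therefore helps only if the model lets the early difference appear as such.

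**The case against.** The strongest reply is that the rehabilitation text describes restriction, not recovery. The sling covers about half of the unmeasured window in both groups, and motion is released in steps, so function may be limited by protocol in both. In the illustration only the fastest case largely disappears by T1, and it needs half of the recovery to be complete within 2 to 4 weeks, while patients are still in the sling. Four assessments in the first postoperative year do describe recovery from month 3 on. All of this stands, and it limits the size of the point.

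Several stronger readings are tempting, but the document does not support them:
- *Much function returns before month 3.* The article gives no early DASH course, and the rehabilitation description does not show this.
- *There are no data from the period.* T0 and T1 bracket it, and the mean change across it is observed.
- *A difference at 3 months might reflect a later divergence.* It cannot: a difference seen at month 3 has arisen by month 3.
- *Recovery times are interval-censored.* That applies to a time-to-event endpoint; the article plans random effect models on the scores.
- *One added visit gives 80% power for the recovery-curve comparison.* A single-visit t-test for 10 points has 80.6% power, but that carries the 24-month difference and its SD to an early visit, and step 6 shows that the result depends on the contrast.

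The sling also affects the remedy. By the article's description, 21 of the 30 DASH items concern difficulty with daily physical activities, so an early score would partly reflect a restriction common to both groups.

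What the reply does not remove is the gap itself, for which the article gives no reason.

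**Conclusion.** The point holds in a limited form. The primary outcome is speed of recovery, and the schedule cannot show the shape of recovery in the first 3 months or any difference that closes by then. It does show the net change from T0 to month 3, any difference that persists to T1, and the course thereafter.

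How much this costs cannot be fixed from the document. On the assumed curves the loss is substantial when recovery is very early and small when recovery is slower. These figures rest on exponential recovery, a common plateau of 40, starting values of 60 to 80, one group twice as fast, and an SD of 19.4 at every visit; only the SD, and a DASH of about 40 after hemiarthroplasty, come from the article. The sample size being set on a 24-month difference is a related mismatch with a speed outcome, but a separate point.

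The trial remains informative without a change. The change is worth making because it is cheap and bears on the headline question.

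**What to change.** Add one mailed DASH, with the pain VAS, between surgery and month 3, for example at or shortly after 6 weeks, by the mail route already set up for T2 and T3. Include it in the longitudinal model with visit as a categorical factor and a group-by-visit term, so that the early difference is estimated directly and is neither averaged over visits nor forced into a linear slope.

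The cost is one questionnaire per patient, 2 × 67 = 134 mailings, with no clinic visit or procedure. The downsides are the added burden and the items that partly reflect the sling; the interpretation of that visit should say so.

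If no early DASH is added, restate the primary outcome as the DASH course from 3 to 24 months and word the conclusions accordingly.
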